### Ethics

All patients will be informed of the objectives of the study and invited to voluntarily participate at the first contact and at the 3 months and 1 year follow-up visit. Patients who will agree to participate will provide oral consent. All information will be kept confidential.

The ObA2 observatory has received the French authority in charge of data protection (CNIL - authorization n°911,201) authorizations necessary for the processing of nominative medical data. Authorizations with the Comité de Protection des Personnes (CPP- number 2018-A01919–46) and CNIL (authorization n° 918,423 (DR 2019–088) have been specifically received for the PAPASépa project.

## Discussion

### Expected outcomes

By integrating a longitudinal dimension and relying on a large cohort, the new knowledge generated by this project will make it possible to identify the barriers and the factors favorable to the outcome of the life pathways, i.e.: 1) information on the elements of the pathway most closely associated with patient functional prognosis, 2) an accurate description of the life pathways, patients with stroke, by defining a typology of these pathways, information currently poorly known, especially on the downstream path, 3) very precise information on the frequency of post-stroke sequelae 3 months and 1 year after the stroke, information currently missing in France.

This information is important for the planning of the offer and thus to the shared and enlightened management of the public policies concerning stroke pathways. Thus, knowledge about the link between the life pathways and functional outcome will bring original information to reduce the impact of stroke by taking into account resources needed meeting the needs of patients and objective information on the inequalities of access to care and on the shortcomings of the healthcare offer.

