#### Patient selection criteria

The inclusion criteria into the PAPASéPA cohort are: inclusion criteria to ObA2 (being over 18 years of age living in metropolitan France, suffering from a recent stroke whose diagnosis was confirmed by a neuro-vascular physician) and as additional criteria, Giving consent to participate to PAPASéPA).

Patients will be identified prospectively as they are included in ObA2. The inclusions will be carried out continuously and prospectively from the date of the beginning of inclusions (planned to be in september 2019) until the required number of subjects is obtained in each strata.

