### Data management and statistical analysis

#### Sample size selection

The primary endpoint is the mRS, measured at 3 months and 1 year after the stroke. Based on data from a pilot study, we assume a prevalence of independence of 51%, dependence of 30% and death of 19%. Several simulations were performed by varying the frequency of exposure to the risk factor studied (very rare to very common). By fixing the risk of first species at 5% and the power of the association test at 80%, to show an odds ratio of at least 2 (odds ratios to move to a higher class: independence to dependence or death, dependence on death), 368 patients should be included to cover a change in exposure to the risk factor studied, ranging from 20% (rare exposure) to 80% (frequent exposure).

The study is stratified on the NIHSS score assessed at inclusion (at the end of the hospital stay for acute episode management) in 3 categories (≤6, 7–16, > 16) and needs to include 368 patients per category of NIHSS or 1104 patients in total (software R v3.3.1).

To account for an estimated 5 to 10% of lost to follow-up, it is necessary to include 1210 patients.

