##### Statistical methods

Qualitative variables will be described in terms of numbers, percentages, and 95% confidence intervals according to the exact binomial distribution. Comparisons will be made by the Chi-square, corrected Chi-square or exact Fisher test. A logistic or polytomial regression model will be used to take into account the adjustment variables.

The quantitative variables will be described in terms of mean, standard deviation, median, extent and interquartile range. Comparisons will be made by Student test, Student test for unequal variances, Wilcoxon test, according to the distribution of the variable of interest.

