### Representativeness of cohort compared to stroke occurring in the Aquitaine region

A total of 13 health facilities are actively involved in the PAPASéPA project. They include all types of stroke facilities: 5 stroke units, 2 hospitals with neurologist and 6 hospitals without a neurologist. They are spread throughout the Aquitaine region (former Aquitaine region). Their annual stroke patients queue ranges from 70 to more than 1000. In 2016, these 13 centers cared for 5230 stroke patients, which represented 68% of strokes registered in the 2016 regional PMSI Aquitaine database. The comparison between the 2016 ObA2 cohort of these 13 centers and the 2016 PMSI stroke database showed similar age and type characteristics of stroke. Everything suggests that these 13 centers make it possible to constitute a cohort of stroke patients representative of the population of patients treated in Aquitaine for stroke.

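### Equal discharge-NIHSS quotas mean that unweighted pooled frequencies, pathway-type shares and inequality comparisons reflect the quota mix, not stroke patients in Aquitaine

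*Protocol article*

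**What the plan says.** All references are to the protocol article.

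- **Sampling.** Under Sample size selection, "The study is stratified on the NIHSS score assessed at inclusion (at the end of the hospital stay for acute episode management) in 3 categories", and the study "needs to include 368 patients per category of NIHSS or 1104 patients in total". Under Patient selection criteria, inclusion runs "until the required number of subjects is obtained in each strata". Severity shares in the sample are therefore set by design.
- **Role of severity.** Study design, under Justification of methodological choices, names initial severity as one of the strongest correlates of functional prognosis, says that it shapes the type of life pathway, and calls it a potential major confounder.
- **Estimator.** Under Statistical methods: "Qualitative variables will be described in terms of numbers, percentages, and 95% confidence intervals according to the exact binomial distribution". Under Analysis plan, the typology comes from hierarchical or latent class clustering. Social and geographical characteristics are then compared between the resulting types with the same descriptive and comparative methods. Weights, standardisation and frequencies by stratum are not mentioned.
- **Claims.** Objectives sets a typology and an inequality analysis for stroke patients in Aquitaine. Expected outcomes promises "very precise information on the frequency of post-stroke sequelae 3 months and 1 year after the stroke" and offers it for planning and public policy. The section on representativeness says that the 13 centres "make it possible to constitute a cohort of stroke patients representative of the population of patients treated in Aquitaine for stroke". Its evidence is that the 2016 ObA2 patients of these centres resembled the regional hospital database in age and stroke type.

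**The concern.** An exact binomial interval treats the patients as a simple random sample from the population described. Here the sample is one third mild, one third moderate and one third severe because each stratum is powered separately. If severity is distributed otherwise among patients leaving the acute stay, a pooled percentage answers a question about an artificial population. A narrow interval around it then conveys precision about the wrong quantity.

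The comparison offered for representativeness cannot repair this. It concerns all 2016 ObA2 patients of the centres, does not look at severity, and predates the quota. Inclusion also takes place at the end of the acute stay, whereas the claim is about all patients treated.

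At stake are the descriptive outputs meant for regional planning: sequelae frequencies, the share of each pathway type, and the social and geographical comparisons between types. The primary association analysis is not at stake.

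**Working it through.** **1. Where the equal split comes from.** Inputs from Sample size selection: 51% independent, 30% dependent, 19% dead; odds ratio 2; alpha 5% (sidedness not stated, two-sided used); power 80%; exposure 20% to 80%. Whitehead's formula for proportional odds, with A = (1 − e)/e and e the exposure prevalence:

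N = 3(A + 1)²(z_α + z_β)² / [A (ln OR)² (1 − Σp³)]

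- At e = 20%, A = 4 and (A + 1)²/A = 6.25; e = 80% gives the same value.
- (1.960 + 0.842)² = 7.849; (ln 2)² = 0.4805; 1 − (0.51³ + 0.30³ + 0.19³) = 0.8335.
- N = 3 × 6.25 × 7.849 / (0.4805 × 0.8335) = 367.5, so 368, and 3 × 368 = 1104.

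Both figures reproduce. The stated 1210 corresponds to a loss of 1 − 1104/1210 = 8.8%, inside the stated 5 to 10%. The 1:1:1 split thus follows from powering each stratum and owes nothing to the regional severity mix.

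**2. Bias of an unweighted pooled percentage.** With natural shares W_h and stratum rates p_h, the target is ΣW_h p_h and the unweighted estimate tends to Σp_h/3. The bias is the difference. It is zero only if the natural shares are one third each, or if departures from one third are unrelated to the rates, in practice if outcomes do not vary by stratum. The article's own statement on severity speaks against the latter.

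The documents give neither W_h nor p_h, so both are **assumptions**, shown as a range. The assumed 30% + 19% = 49% for dependence or death cannot calibrate them: the pilot population is not described, and the same figures are used for every stratum.

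Outcome: dependence or death; rates in the order ≤6, 7–16, >16. Entries are the target, with the bias in points.

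| Natural shares (%) | Weak 40/50/60% (unweighted 50.0%) | Moderate 35/60/85% (unweighted 60.0%) | Strong 25/75/95% (unweighted 65.0%) |
|---|---|---|---|
| 50/30/20 | 47.0 (+3.0) | 52.5 (+7.5) | 54.0 (+11.0) |
| 60/25/15 | 45.5 (+4.5) | 48.75 (+11.25) | 48.0 (+17.0) |
| 70/20/10 | 44.0 (+6.0) | 45.0 (+15.0) | 42.0 (+23.0) |
| 80/14/6 | 42.6 (+7.4) | 41.5 (+18.5) | 36.2 (+28.8) |

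Example: 0.50 × 35 + 0.30 × 60 + 0.20 × 85 = 52.5, against (35 + 60 + 85)/3 = 60.0.

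**3. Nominal precision.** 1.96 × √(0.5 × 0.5/1104) = 2.9 points. The smallest bias in the table about equals this, and the others exceed it.

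**4. Price of weighting.** Kish design effect for equal strata: 3ΣW_h². For 50/30/20 it is 3 × (0.25 + 0.09 + 0.04) = 1.14. The other three mixes give about 1.33, 1.62 and 1.99. Effective n = 1104/deff = 968, 827, 681 and 555. The stratified half-width, 1.96 × √(ΣW_h² p_h(1 − p_h)/368), is 2.6 to 4.1 points over the twelve scenarios. Within one stratum at p = 0.5 it is 1.96 × √(0.25/368) = 5.1 points.

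**The case against.** Pooling without weights is inferred. Statistical methods is generic text on describing variables and does not say that the strata are combined. The cohort is described as divided into three strata, each powered separately, which fits reporting by stratum, where no severity-mix bias arises. A separate statistical analysis plan is announced and could add weights. The same section foresees regression with adjustment variables, so adjusting the inequality comparison for severity remains open. Frequency estimation is not a listed objective, and the representativeness sentence can be read as a claim about centre coverage.

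Much of this stands, and it is why the point is confined to figures pooled over strata. It does not remove the point. The article names an interval method that ignores the design, and it claims regional precision and representativeness on evidence that leaves out both severity and the quota. Neither claim is limited to strata or to centre coverage.

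Stronger readings that a reader might infer, and that the documents do not support:

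- *That severe patients are over-represented, and dependence and death overstated, by a known amount.* No natural severity distribution or stratum-specific rate is given. Even the direction assumes a population milder than one third in each stratum.
- *That the typology is invalid.* Larger severe strata may help to detect less common types. It is the type shares and pooled comparisons between types that carry the quota mix.
- *That the primary analysis is biased.* Stratum-specific or correctly specified severity-adjusted odds ratios are not distorted by the quota.
- *That in-hospital deaths are a stated exclusion.* This is a plausible consequence of inclusion at the end of the stay, but the article does not say it.

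**Conclusion.** The concern holds for descriptive and comparative results pooled over strata. Equal quotas, the acknowledged role of severity and unweighted percentages with simple-random-sample intervals cannot together support frequencies, type shares or inequality comparisons for stroke patients in Aquitaine. The representativeness statement does not extend to this sample.

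The existence of the bias follows from the text, unless the natural shares happen to be one third each or outcomes do not vary by stratum. Its size does not follow: +3 to +29 points for dependence or death is a range over assumed shares and gradients, to be set against a nominal half-width of about 3 points. The change should be made, but the main objective does not depend on it.

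**What to change.** 1. Report sequelae frequencies and pathway-type shares by NIHSS stratum.
2. For any pooled figure, and for the social and geographical comparisons, weight patients to the discharge-NIHSS distribution of all eligible ObA2 patients over the recruitment period. Use design-based intervals in place of exact binomial ones.
3. Before that, reconcile where discharge NIHSS is held. The text on the ObA2 extraction under Data sources lists it among the ObA2 items. Table 1 lists it as ad hoc collection, and its ObA2 footnote names only NIHSS at admission. If ObA2 does not hold it for all eligible patients, the weights cannot be computed and reporting should be by stratum only.
4. Limit the claims under Expected outcomes and in the representativeness section to the source centres and to patients included at the end of the acute stay.
5. Leave the clustering and the severity-adjusted or stratum-specific association models unweighted.

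The cost is a count table from ObA2, if the variable exists there, plus changes of wording. The statistical price is a design effect of about 1.1 to 2.0 (effective n about 968 down to 555 of 1104) for pooled figures, or half-widths of up to about 5 points within strata. The counts are easiest to secure while recruitment is running.

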### Feasibility of the proposed approach

In order to help develop and ensure its feasibility, all the necessary teams and skills are involved in the project: neurologist clinicians, researchers in health services research who know the databases and have the skills in the SNDS data processing, an operational team from the ObA2 cohort, and finally medical informatics teams who will be able to develop data-visualization methods for pathway analysis.

Moreover, the ad hoc collection of sequelae has been tested in a pilot survey and showed its feasibility, its acceptability for patients and caregivers.

Concerning the technical and ethical conditions of the links between the existing databases, respective reconciliations of these databases have already been tested and will be carried out in a secure manner after prior approval by the CNIL (Commission Nationale Informatique et Libertés).

### Justification of methodological choices

#### Study design

Research on pathways must integrate a longitudinal dimension and rely as much as possible on large cohorts. Our project is based on a prospective multicenter cohort (ObA2 cohort), following the life pathway and sequelae of stroke patients for 1 year after the acute episode. Such a design will allow to approaching the place and the role of the temporal and spatial pathway dimensions on the functional prognosis of patients with stroke.

The project relies on data from ad hoc collection and extraction of data from three existing databases. The combination of these sources of information will allow the understanding of the heterogeneity of the life pathway of stroke patients as a whole, in all its dimensions, temporal and spatial, from the acute episode up to 1 year of follow-up.

The cohort will be divided into three strata according to the severity of the patient’s initial clinical condition, as measured by the NIHSS score at hospital discharge. The initial severity of stroke is one of the variables most strongly associated with functional prognosis after stroke and influences the type of life pathway of stroke patients. Thus, it constitutes a potential major confounding factor in the relationship between stroke and sequelae. The NIHSS score at the exit was preferred to the NIHSS at entry because the patient’s pathway is more strongly influenced by the level of hospital dependence at discharge than at entrance, major progress being potentially made during the acute phase of stay.

Other major potential confounding factors, including clinical patient characteristics and elements of the acute phase care pathway, already identified as predictive factors on functional prognosis, are collected and considered in the data analysis (variables related to the patient’s previous condition, variables related to stroke and variables related to the patient’s care pathway prior to hospitalization).

#### Management of the evolving character of the events collected

The three times ad hoc collection and the continuing and prospective collection of pathway events from existing databases will allow the analysis and the management of the evolving nature of the main study issues: sequelae, socioeconomic environment and health events during the year after stroke. This evolutional process is major to describe because it modifies the patient pathway itself. The evolving character of the sequelae throughout the post-hospital journey requires the use of adapted statistical model. This polyptic regression model will analyze the factors associated with sequelae at 1 year, while taking into account the degree of these sequelae at 3 months.

#### Life pathways: perimeter

Despite a collective awareness, as to the inadequacy of the organization of the health system, different realities exist regarding the notion of pathways [38, 44–46].

In the PAPASéPA project, we adopt the global conception of the life pathway of stroke patients. All the elements of care but also the context of life in which the patient evolves (family and social environment, financial aid, income, adaptation of lifestyle and environment, etc.…) will be taken into account.

However, life pathway data are mainly collected during phone interviews using closed-ended questions. Responses may lack of precision and could be not exact. In order to obtain a more precise description of these life pathways access to databases such as the CDAPH (Commission for the rights of disabled persons to independence) would be necessary. This database, which collects all the social benefits people receive, will only be available in the coming years.

#### Types of measured sequelae and tools taken to measure them

The sequelae explored include all impairments (cognitive disorders, anxiety disorders and fatigue), activity limitations (residual and recuperated functional possibilities) and participation restrictions (social consequences) resulting from stroke based on the ICF (International Classification of functioning disability and health). The variables sphincteric disorders and dysphagia will be collected from the Barthel and mRS scales respectively.

While motor impairment, ataxia or aphasia are easily recognized complications, other deficiencies, such as cognitive impairment [47], depression or fatigue are also frequently reported but under evaluated among stroke survivors. These so-called “invisible” deficiencies are thought to contribute to the participation restrictions in daily life activities and impaired quality of life [48]. To address this lack of information, we adopted a multi-dimensional approach to assess the frequency and type of deficiencies with a focus on their daily-life consequences (limitations of activities, participation restrictions) in a cohort of stroke survivors during 1 year after stroke.

The scales measuring each of the dimensions explored are based on elements of feasibility, frequency of use, validation and application condition.

#### Main outcome

The main outcome is the modified Rankin score in three categories. This score gives an overall measure of the level of functional dependence, integrating the ICF components of body function, activity to participation. This is the reference measure found in many publications. Its use in this project will allow national and international comparisons. The defect of reproducibility of its measurement will be taken into account in our project, as following: 1) measure realized by only three people trained according to the good practices of use of the scale before the start of the project, 2) the IRC measuring the mRS during the follow up are not those who included them.

### Representativeness of cohort compared to stroke occurring in the Aquitaine region

A total of 13 health facilities are actively involved in the PAPASéPA project. They include all types of stroke facilities: 5 stroke units, 2 hospitals with neurologist and 6 hospitals without a neurologist. They are spread throughout the Aquitaine region (former Aquitaine region). Their annual stroke patients queue ranges from 70 to more than 1000. In 2016, these 13 centers cared for 5230 stroke patients, which represented 68% of strokes registered in the 2016 regional PMSI Aquitaine database. The comparison between the 2016 ObA2 cohort of these 13 centers and the 2016 PMSI stroke database showed similar age and type characteristics of stroke. Everything suggests that these 13 centers make it possible to constitute a cohort of stroke patients representative of the population of patients treated in Aquitaine for stroke.

### Outlook

Healthcare is changing towards more patient focused care. It’s an international phenomena. The sharing of information systems and the easy sharing of data between professionals is a powerful vector of this evolution, which is conducive to the development of new methodologies for data analysis. The study of the complete patient-centered hospitalization journey in the year following the acute stroke episode requires a longitudinal approach to sequences of health events ordered over time. The reconstitution of these pathways will be based on the chaining of the different hospital stays of the patient, from the first hospitalization during the acute episode of stroke to 1 year of follow-up after the stroke. This project will provide a first overview of the life pathway of stroke patients and have a description of the existing to provide elements in order to propose solutions to the problems posed.

## Data Availability

Not applicable.

## Abbreviations

APA: Allocation Personnalisée d’Autonomie
ARS: Agence Régionale de Santé
CCTIRS: Comité Consultatif sur le Traitement de l’Information en matière de Recherche dans le domaine de la Santé
CDAPH: Comission des droits et de l’autonomie des personnes handicapées
CIF: Classification Internationale du Fonctionnement, du Handicap et de la Santé
CIQ-R: Community Integration Questionnaire-Revised
CNIL: Commission Nationale Informatique et Libertés
EQ5D-3 L: Quality of life EuroQol five Dimension EQ5D-3 L questionnaire
ESD: Early Supported Discharge
FSS: Fatigue Severity Scale
F-TICS: French Telephone Interview for Cognitive Status Modified
HAD: Hospitalisation A Domicile
HADS: Hospital Anxiety and Depression Scale
IADL: Instrumental Activity of daily living
IB: Barthel Index
IDS: Institut des Données de Santé
IRC: Infirmière de recherche Clinique
LHS: London Handicap Scale
MRS: Modified Rankin Scale
NIHSS: National Institutes of Health Stroke Scale
ObA2: Observatoire Aquitain des accidents vasculaires cérébraux
PAPASePA: Parcours des Patients victimes d’accident vasculaire cérébral et Séquelles Post-Accident vasculaire cérébral
PCH: Prestation de Compensation du Handicap
PMSI: Programme de Médicalisation des Systèmes d’Information
QALY: Quality-ajusted life years
SNDS: French National Health Data System (SNIIRAM, PMSI and CépiDC)
SNIIRAM: French National Health Insurance Database
WHO-ICF: World Health Organization’s International Classification of Functioning, Disability and Health
